##### Control Condition

The information-only control group receives the same number of MMS messages and interactive features as the intervention group, over the same amount of time, but does not receive motivational or behavioral skills content. The content, outlined in Figure 2, covers information on physical, social, mental, and sexual health.

**Figure 2. F2:**
[figure not shown]
A comparison of SMS text messaging sent in the control and treatment arms and the resources provided in either arm. LGBTQ: lesbian, gay, bisexual, transgender, queer, and questioning; MMS: multimedia messaging service; PEP: postexposure prophylaxis; PrEP: pre-exposure prophylaxis; STI: sexually transmitted infection.

### Feedback From Topical Experts

Prototypes of the intervention content and interactive updates underwent review and feedback from a youth advisory council and adult informants as described below.

#### Youth Advisory Council

To ensure SGM adolescent perspectives were reflected in the intervention, we recruited a Youth Advisory Council (YAC) of 24 lesbian, gay, bisexual, transgender, queer, and questioning (LGBTQ+) teens aged 14‐18 (mean 16.6) years. Eligibility criteria included (1) identifying as a sexual and/or gender minority; (2) being 13‐18 years old; (3) reading English at an 8th-grade level or higher; (4) passing a capacity to assent or consent assessment and providing informed consent; and (5) residing in the United States or its territories. YAC members were recruited online via paid social media and online registries. Identity verification procedures were used to confirm eligibility and decrease the likelihood of enrolling impostor participants. This included a video call with a study team member to verify personal information and comprehension of study details [37-39]. Following a virtual orientation session conducted via Zoom (Zoom Communications, Inc), eligible youth were invited to a private Discord (Discord Inc) server, an instant messaging platform that supports MMS, voice, video, and multimedia communication. Members received US $30 per month, with the opportunity to earn an additional US $60 per quarter for optional activities (eg, creating social media content and testing interactive features). For further details on the YAC’s structure and acceptability as a human-centered design approach, see [40].

Each YAC member received components of the adapted intervention in different delivery formats (eg, messages, chatbot, and polls). Members were asked to provide feedback in the Discord server to enhance acceptability, including salience, tone, inclusivity, and engagement with the intervention. Youth also participated in “Wizard of Oz” testing [41], a prototyping approach often used in human-computer interaction and design research, in which study staff manually sent draft versions of messages to YAC members. Participants then gave feedback on the intervention during structured conversations in the Discord server. This enabled the study team to simulate the intervention experience and gather real-time youth feedback on intervention content and features prior to investing considerable time in software development.

#### Interviews With Potential Implementers

To understand potential implementers’ perspectives on the intervention before completing software development and final content edits, we recruited 30 adult participants for 1-hour individual Zoom interviews. Eligibility criteria included being (1) aged 18 years and older, (2) residing in the United States or territories, and (3) working in one of the following areas: adolescent HIV prevention and care (eg, adolescent medicine); digital health; and/or in an organization that uses digital approaches to reach adolescents for services, education, or community programs.

Interviews followed a semistructured guide and were accompanied by a PowerPoint (Microsoft) presentation that outlined the proposed intervention’s target population, intended outcomes, study timeline, sample messages, interactive tools and features (see Figure 2), and proposed implementation models (eg, referral-based vs licensing). Participants were asked for feedback on the content, structure, and delivery of the intervention and to assess its implementation within their organizational settings. Where applicable, depending on the participant’s workplace or experience, additional questions explored strategies for enhancing linkage from digital interventions to HIV and STI and sexual health services. Data were analyzed using qualitative content analysis of the suggested adaptations guided by the Framework for Reporting Adaptations and Modification to Evidence-Based Interventions (FRAME) and FRAME-Implementation Strategies [42,43].

#### Integration of Youth and Adult Feedback

Key themes from the interviews were discussed during internal team meetings, and follow-up questions about intervention content, interactivity, structure, and delivery were posed to the YAC. We focused on areas where perspectives of adolescents and prospective implementers differed, and insights from both groups were used to finalize the content and features of the intervention. The research team finalized intervention content and the delivery of the interactive elements based on our synthesis of this information, and the software development team began finalizing and programming intervention features described in Figures 2 and 3.

**Figure 3. F3:**
[figure not shown]
Recruitment, enrollment, and study time points. SHER: Sharing Health Education Resources.

### Software Development and Functionality Testing

An in-house research software development team created the bespoke intervention software for the project and is responsible for end-to-end quality assurance testing, troubleshooting, maintenance, optimization, and system hardening (making the system more secure by fixing weaknesses and reducing risks) for the duration of the project. The intervention software and administrative dashboard were developed with study team input that was informed by experience developing prior digital interventions as well as youth and potential implementers’ perspectives. Once content was finalized, functionality testing began. The research team first conducted internal alpha testing (n=14) of both the intervention and control conditions. This phase of testing helped identify bugs, confirm randomization procedures, and ensure functionality of interactive components, allowing the team to engage directly with the MMS delivery platform and make minor adjustments to the intervention content (eg, addressing typos). Minimal errors were identified in this phase.

To streamline data collection, the study team opted to conduct a single round of beta testing, with 3 simultaneous cohorts of testers receiving the intervention over 3 months. A total of 19 adolescent beta testers recruited in the same manner as the YAC members and who reflected the study population participated in this phase, receiving either treatment (n=10) or control (n=9) arm messages over 6 weeks. These beta testers were invited to a private Discord server separate from the YAC to offer feedback on the intervention in real time. Beta testers completed polls, open-ended questions, and prompts specifically designed to evaluate program features and ensure that the technology, such as message delivery, timing, and formatting, was functioning as intended. Bugs were reported in real time through Discord, documented in an Excel file by study staff, and relayed to the software development team for resolution. To further assess functionality and user experience, beta testing concluded with brief phone interviews focused on identifying technical challenges, evaluating the interactive components, and gathering suggestions to enhance engagement. This process confirmed the feasibility and acceptability of the intervention prior to the launch of the RCT in Aim 2.

### Approach for Aim 2

This RCT was initially registered on ClinicalTrials.gov on October 18, 2023 (NCT06096519) and reporting standards from SPIRIT (Standard Protocol Items: Recommendations for Interventional Trials) 2025 were followed [44] (Checklist 1).

### RCT Launch (June 2024-February 2025)

#### Overview

The recruitment, enrollment, and study time points across both arms of the study are outlined in Figure 3. The RCT was launched in June 2024, and initial eligibility criteria were (1) male gender identity or male sex at birth, (2) ever had anal sex with a partner assigned male at birth, (3) identify as a sexual or gender minority or are questioning their sexuality, (4) aged 13‐18 years, (5) read in English at a 6th grade level, (6) never received an HIV or STI test, (7) HIV negative or unknown status, (8) own a cell phone with an unlimited MMS plan and plan to have the same number during the study, (9) can provide informed consent, as shown on a capacity to consent assessment [45], and (10) live in the United States or US territories. Like the YAC, participants initially were recruited predominantly via social media platforms, where they viewed advertisements that directed them to a study information page, followed by a brief online screener and a required identity verification call. Informed consent and assent are completed online by the participant, followed by a video chat with study staff to answer questions and/or address concerns about the study prior to enrollment. All personal information from potential and enrolled participants is collected remotely and stored in REDCap (Research Electronic Data Capture; Vanderbilt University) and private university servers.

#### Randomization

After screening for eligibility, verifying identity, and completing the baseline survey (described in Assessment below), enrolled participants were randomly assigned to receive SHER or the information-only control arm (1:1 allocation). Randomization is stratified by age (minors vs 18- and 19-year-olds), sex assigned at birth, prior condomless penetrative sex with a partner assigned male at birth, and gender identity at baseline to ensure sufficient representation by these characteristics in each condition to conduct exploratory analyses of potential group differences in outcome effects. After incorporating changes to eligibility criteria described below, HIV testing history (never or ever received an HIV test) was added as a stratification variable to account for the inclusion of individuals that have previously been tested. A computerized minimization technique [46-49] is implemented to reduce the likelihood of imbalance across study arms with respect to our stratification variables. Personnel who enroll the participants do not have access to the random allocation sequence. Participants are blinded and are only told they are testing one of 2 versions. Participants will not be unblinded until after all study data are collected.

#### Recruitment Challenges (July 2024-August 2024)

Initial recruitment was relatively slow and costly, with only 24 participants enrolled over a 5-month period at a cost of US $273.05 per participant. This cost was over 4 times the cost per enrollment (US $61.22) using the same Meta advertising strategy as a similar digital sexual health clinical trial reaching a nearly identical population in years 2018‐2020 [50,51]. The study team hypothesized that this was largely due to policy changes implemented by Meta in 2023 that increased restrictions on targeted advertisements to minor adolescent users (eg, prohibited from targeting minors based on sexual or romantic interest in same-sex partners) [52].

In July and August 2024, the research team observed a surge in eligible screener entries. However, after nearly all these individuals failed identity verification calls for similar reasons, it became clear that they were likely “impostor participants” [53]. Given that the new group chat feature enabled adolescent participants to interact with other participants, additional procedures were implemented to protect participant safety and data integrity. A modification was submitted to the institutional review board (IRB) in August 2024 to update the screening and verification procedures with more robust methods, such as requiring photo identification (eg, school ID or government ID), additional verification questions, and careful screening of photo IDs for AI generation and editing. During the one-month period of IRB submission and review, online study advertising was paused and resumed at the end of August 2024. These procedures, though time-consuming, appeared to act as an effective deterrent.

#### Changes to Inclusion Criteria (March 2025)

After several months of recruitment, it became clear that the recruitment procedures and inclusion criteria that were used in the study team’s prior intervention research with SGM adolescents were not yielding a robust sample [51]. The study team attempted to reduce bottlenecks to enrollment by reducing the number of steps from advertisement click to screener completion, reducing the number of screener questions, and making the study information page more engaging. However, the most substantial obstacle to enrollment appeared to be the stringent inclusion criteria. Following consultation with the investigative team and the study’s program officer at the US National Institutes of Health, several changes were made.

First, criteria were expanded to include participants that had ever had oral sex, but not penetrative sex, with a partner assigned male at birth. Our screening data showed that 404 individuals had been excluded from participation based on sexual experience alone. Evidence suggests most adolescents initiate oral and penetrative sex within the same 6-month period [54]. Therefore, individuals with only oral sex experience were presumed likely to engage in behaviors that would warrant HIV testing during the 9-month study period, as shown in the survey timeline depicted in Figure 3. In addition, 174 individuals had been excluded during initial recruitment between July 2024 and February 2025 based on prior experience with HIV and STI testing. We thus chose to include individuals who had previously been tested, were not taking PrEP (as PrEP regimens require roughly quarterly HIV testing), and could benefit from HIV testing based on clinical guidelines.

Next, age criteria were expanded to include 19-year-olds, who are still in the developmental stage of adolescence yet are more likely to be sexually experienced and still report low HIV and STI testing rates [55]. Thirteen individuals were excluded during the initial recruitment period based on being 19 years of age. Finally, in June 2025, we expanded the intervention to include cisgender sexual minority (eg, lesbian, bisexual, pansexual, and queer) girls who reported vaginal or anal sex with a partner assigned male at birth. Expanding criteria to be inclusive of more gender identities was favored by community partners and prospective implementers, as this would serve a greater proportion of their client population and reach a group who could benefit from but may not be targeted for HIV and STI screening [56].

Before implementing these expanded inclusion criteria, the study team audited and adapted the intervention content to ensure relevance and appropriateness for the newly included demographics. Enrollment rapidly increased after relaunching the study with updated criteria in March 2025, and cost per enrolled participant was reduced to US $70.61 as of September 2025, which is consistent with the team’s previous work with SGM adolescents in digital health studies [51].

#### Changes to Sample Size (August 2025-March 2026)

In summer 2025, although the enrollment rate increased, it was not enough to compensate for the time lost in the earlier months of the RCT, and the team was experiencing several additional challenges. First, there was uncertainty about whether the project would continue to be funded by NIH due to changes in federal funding priorities, and the grant budget had been reduced substantially. Furthermore, RCT and Aim 3 activities were occurring simultaneously due to the recruitment delays, requiring study staff to manage competing priorities. In addition, the longer recruitment lasted, the more costs would be incurred for advertising and retention. These factors led the investigative team to explore the feasibility of reducing the sample size to conserve resources and ensure completion of the trial before the end of the grant period.

Power calculations were performed using nominal type I error rates (α=.05) and assumed a 1:1 allocation to each study arm and identical arm-specific retention rates. The assumed HIV testing rate for control participants at the final time point was 28% based on previous findings from the G2G pilot study [26]. The original sample size proposed in the grant (n=360) was chosen to power comparisons at the end of the trial. Assuming 80% retention, the study would be 81% powered to detect a small to medium intervention effect for self-reported or objective HIV testing. Revised power calculations were conducted in August 2025 by a biostatistician. It was concluded that, assuming study endpoint retention rates of 90% or higher, the study’s target sample size could be reduced from 360 to 310 and maintain the 80% power to detect differences between the intervention and control groups at the same magnitude that was targeted in the original power analysis. At the time of these analyses, study retention was at or near 90% and, in March 2026, exceeded 90%. The sample size reduction and expanded inclusion criteria will likely limit the ability to conduct adequately powered subgroup analyses, so those analyses will be treated as exploratory. However, maintaining the higher targeted retention rate should allow for mediation analysis at similar power levels as the originally targeted sample size. Assuming these recruitment rates hold, we anticipate completing recruitment by June 2026 and retention efforts by January 2027.

During the October 2025 Data Safety Monitoring Board (DSMB) meeting, we informed board members about our plan to reduce the sample size. The DSMB unanimously agreed this was the appropriate course of action, noting our high retention rates exceeding 90% and the prolonging of recruitment to obtain our original sample size was unnecessary. The principal investigator also sought approval from the NIH in October 2025, which was granted in March 2026, following the submission of our annual research performance progress report.

#### Pre- and Postlaunch Protocol Modifications

In summary, our study originally aimed to enroll 360 participants between the ages of 13 and 18 years who were assigned male at birth or had a masculine gender identity, had not previously obtained an HIV test, and had engaged in penetrative sex with a partner assigned male at birth. In March 2025, we expanded the criteria to include 19-year-olds, individuals assigned female at birth who were at elevated risk for HIV, and those who had previously obtained an HIV test but at the time of enrollment were eligible for another HIV test. Despite implementation of multiple recruitment strategies, recruitment continued to progress slower than anticipated. In 2026, the study team therefore reduced the sample size to 310, having determined that statistical power would be retained provided retention rates remained at or above 90%, which was highly likely based on interim retention rates. All modifications were approved by the IRB and NIH prior to implementation, and ClinicalTrials.gov was updated accordingly.

#### Assessment

Measures (Table 1) are collected at baseline, immediately postintervention, and 3- and 6-month postintervention. Baseline measures assess HIV and STI testing behaviors, HIV-related knowledge, motivation, and behavioral skills, sociodemographic characteristics, and sexual history. All participants complete an assessment immediately postintervention (6-week) to evaluate intervention acceptability adapted from a previous digital sexual health study [50,57]. At 3-month postintervention, HIV information, motivation, and behavioral skills [58] and HIV and STI testing history are assessed again. Then, we follow adolescents for 6 additional months (Table 1) to allow enough time to elapse for participants to engage in HIV testing. The final 6-month postintervention survey assesses the same constructs as the 3-month survey. Finally, qualitative interviews with participants from treatment and control arms (n=20 each), who demonstrate low and high engagement in SHER (n=20 each) will further assess acceptability and completion barriers. Level of engagement is defined by the number of prompts (ie, quizzes and polls) that participants responded to during the intervention (low engagers ≤9 responses, high engagers >9 responses).

**Table 1. T1:** Randomized controlled trial (RCT) outcome measures: operationalization and schedule.

Constructs	Measures/operationalization	Measurement timeline						
		Baseline	3 weeks	6 weeks	3 months	6 months	7.5 months	9 months
HIV testing (primary)	Self-reported HIV testing or objective proof of HIV testing in the previous 3 months [51]	✓	✓		✓	✓	✓	✓
STI^a^ testing (secondary)	Self-reported history of testing for STI in the previous 3 months [51]	✓	✓		✓	✓	✓	✓
PrEP^b^ (secondary)	Self-reported at the time of the baseline assessment and past 3-month PrEP use, and willingness to use PrEP [59,60]	✓				✓		✓
Sexual experience history (secondary)	Lifetime and past 3 month sexual experiences, including condomless anal sex partners [61]	✓				✓		✓
Condom use, intentions, and self-efficacy (O)^c^	Condom Use Intentions Scale–11 items; Condom Use Self-Efficacy Scale–5 items; Adapted condom errors questionnaire–15 items [62-64]	✓				✓		✓
HIV knowledge (mediator)	Knowledge of HIV transmission and prevention [65]	✓				✓		✓
Motivation and behavioral skills (mediator)	Motivation (eg, motivation to improve sexual practices), self-efficacy to access HIV testing and prevention methods, social norms (eg, partners', friends’, or family members’ opinions about condom use), and behavioral skills (eg, negotiating condom use) [63]	✓				✓		✓
Behavioral health (O)	Self-reported substance use history, perceived social support, internalized stigma, anxiety, depression, and stress [50,51,66]	✓				✓		✓
SHER^d^ intervention acceptability and tolerability (O)	Intervention impact, usefulness, engagement, usability [50,51]			✓				
Demographics (moderator)	Self-reported age, gender identity, sexual orientation, race and ethnicity, education, socioeconomic status, and rural versus urban [67]	✓						
Dose and engagement (moderator)	System-captured data on intervention dose and engagement (eg, number of texts sent to buddy, number of links clicked, and number of times chatbot used)			✓				

a STI: sexually transmitted infection.

b PrEP: pre-exposure prophylaxis.

c O: other measure.

d SHER: Sharing Health Education Resources.

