This study was motivated by the question of whether the G2G intervention, if updated and repackaged to focus more on HIV testing, could be effective among a broader group of SGM adolescents who may benefit from HIV testing based on their sexual history. First, we aimed to systematically adapt G2G’s content and delivery to refocus the content on HIV testing as a primary outcome [25-27]. We also sought to reflect significant advancements since the pilot RCT in digital technologies, HIV prevention science, and changes in youth and SGM culture, and to make the intervention content more inclusive of SGM adolescent populations underrepresented in HIV prevention and testing research [32]. Our second aim was to evaluate the intervention’s effectiveness on the new primary outcome of HIV testing and secondary outcomes related to sexual health care engagement, such as PrEP uptake and STI testing, via a nationwide RCT among SGM adolescents. We hypothesized that participants in the intervention condition would be more likely to report HIV testing at least once during the 9-month study period than participants in the control condition. Finally, our third aim engaged experts and adolescents to identify key strategies for reaching and engaging SGM adolescents for digital sexual health interventions in real-world settings. This study is in progress, and of note, after the study launched, various challenges led to modifications of study activities originally proposed in the grant, which will be described in this protocol paper.

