### Outcome Measures

Our primary effectiveness outcome of HIV testing is measured using self-report and objective proof (eg, screenshot or photo of HIV testing results uploaded to REDCap, our survey software) while secondary effectiveness outcomes (eg, PrEP uptake and STI testing) are measured via self-report only. We remind all adolescents across study arms at multiple time points (consent, ID verification call, and active or control arm messages related to HIV testing, and boosters) to retain evidence of testing. As some may not notify us immediately, each follow-up survey asks for testing experiences since the prior assessment. Those who report being tested are prompted to securely upload evidence of their HIV or STI test via a participant-specific REDCap link in line with procedures from prior work [68,69]. If any participants report testing positive for HIV or STIs, a staff member will promptly contact the participant and link them to care.

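### The primary outcome has two conflicting recall periods, one of which would let the 3-week survey pick up HIV tests done before randomisation

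*Protocol article*

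**What the plan says.** Two places in the protocol article define how HIV testing, the primary outcome, is asked about.

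- Table 1 (Assessment) uses "Self-reported HIV testing or objective proof of HIV testing in the previous 3 months". The row is ticked at baseline, 3 weeks, and 3, 6, 7.5 and 9 months, with no different wording for any of them.
- Outcome Measures says "each follow-up survey asks for testing experiences since the prior assessment".

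The hypothesis in the Introduction is that SHER participants "would be more likely to report HIV testing at least once during the 9-month study period". Quantitative Analysis describes a mixed logistic model using baseline and two follow-ups, labelled 3-month and 6-month. It names neither the 3-week nor the 7.5-month survey.

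On timing, Randomization states: "After screening for eligibility, verifying identity, and completing the baseline survey (described in Assessment below), enrolled participants were randomly assigned". On earlier testing, the launch criteria required that a participant had "never received an HIV or STI test". The March 2025 section then says "We thus chose to include individuals who had previously been tested", and the later summary of modifications describes these entrants as "those who had previously obtained an HIV test but at the time of enrollment were eligible for another HIV test".

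**The concern.** A recall period decides which tests count as events. A fixed three-month look-back and a look-back to the last survey classify the same test differently whenever surveys are not three months apart, and three of the five follow-ups come less than three months after the previous HIV-testing survey by a clear margin or are themselves that close to baseline.

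Two things are at stake. A fixed look-back at 3 weeks reaches well before randomisation, so it can bring in tests that neither arm could have influenced. A look-back to the last survey avoids that, but each late survey then covers only six and a half weeks, so an analysis that uses only some of the surveys loses the tests reported at the others. If the conflict is still open when the data are analysed, someone must choose between two definitions of the primary outcome at that point.

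**Working it through.** **Step 1: the windows.** Inputs: survey times from Table 1, three months taken as 13 weeks, and randomisation at week 0 straight after the baseline survey. Under Table 1 the window starts at survey week minus 13. Under Outcome Measures it starts at the previous survey, taken here as the previous one that asked about HIV testing (the 6-week acceptability survey is not ticked for it).

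| Survey | Table 1 (weeks) | Since previous HIV-testing survey (weeks) |
|---|---|---|
| 3 weeks | -10 to 3 | 0 to 3 |
| 3 months | 0 to 13 | 3 to 13 |
| 6 months | 13 to 26 | 13 to 26 |
| 7.5 months | 19.5 to 32.5 | 26 to 32.5 |
| 9 months | 26 to 39 | 32.5 to 39 |

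The rules agree at 6 months and nearly agree at 3 months. They differ at 3 weeks (13 against 3 weeks) and at 7.5 and 9 months (13 against 6.5 weeks each). Only the 3-week survey under Table 1 reaches before randomisation, by 10 of 13 weeks (77%). Those 10 weeks also lie inside the baseline look-back.

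**Step 2: does it touch the planned model?** The two named follow-ups could be months from baseline or months after the intervention. The Assessment text calls the final survey 6 months postintervention and says the mediators are measured at the 3-month and 6-month postintervention surveys. Table 1 ticks the mediators at 6 and 9 months, so those columns are the likely match, but this is an inference.

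- Under Table 1, the windows on that reading are weeks 13 to 26 and 26 to 39. On the months-from-baseline reading they are weeks 0 to 13 and 13 to 26. Neither reaches before randomisation.
- Under Outcome Measures, the 9-month survey covers weeks 32.5 to 39 only. Tests in weeks 26 to 32.5 (months 6 to 7.5) are reported at 7.5 months and are lost to the model unless that report is carried in.

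**Step 3: illustrative size if 3-week reports feed an ever-tested endpoint.** The article gives no numerical effect, so it is back-solved from the original power statement in the sample-size section: 360 x 0.80 = 288, or 144 per arm, 28% in control, 81% power, two-sided 0.05, pooled two-proportion test. This gives 44.0% under SHER, a difference of 16.0 points and an odds ratio of 2.02.

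Reproducing the revised figure: 310 x 0.90 = 279, or 139.5 per arm. With mean rate 0.360, the standard error is 0.0575 under the null and 0.0567 under the alternative. Then z = (0.1598 - 1.96 x 0.0575) / 0.0567 = 0.83, so power is 79.8%, against the stated 80%.

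Now let a share q of both arms have a pre-randomisation test inside the 3-week window, so each rate p becomes p + (1 - p)q. The article gives no value for q.

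| q (assumed) | Control | SHER | Odds ratio | Power |
|---|---|---|---|---|
| 0% | 28.0% | 44.0% | 2.02 | 79.8% |
| 2% | 29.4% | 45.1% | 1.97 | 77.5% |
| 5% | 31.6% | 46.8% | 1.90 | 74.1% |
| 10% | 35.2% | 49.6% | 1.81 | 68.3% |

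**The case against.** The strongest reply is that Outcome Measures describes the question actually asked, while Table 1 is a summary row whose three-month wording suits baseline, where there is no earlier survey. If so, no pre-randomisation test is collected at follow-up and only a table cell needs rewording. That may be right, but the article does not say so, and the Outcome Measures rule brings its own gap before the 9-month survey.

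Several stronger readings are tempting, and the documents do not support them.

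- *The primary analysis counts pre-randomisation tests.* Quantitative Analysis does not name the 3-week survey, and no reading of its two follow-ups in Step 2 reaches before randomisation under Table 1. The problem arises only if the hypothesis of at least one test during the study is built from all follow-up reports.
- *Power will fall to 68% to 77%.* The share q is assumed. Participants enrolled under the launch criteria had never been tested. Later entrants had to be due for another test, and the Introduction cites screening intervals of a year or of 3 to 6 months. If those were applied, a test in the prior 10 weeks would be rare, though no minimum interval is stated. The 28% is also a final-time-point rate, so applying it to an ever-tested endpoint is itself an assumption.
- *Overlapping windows count one test twice.* For a yes/no endpoint of at least one test, a test reported at both 7.5 and 9 months is still one event.
- *Table 1 fails to cover the study period.* Its 3-, 6- and 9-month windows together run from month 0 to month 9 when surveys are on time. A late survey can open a gap, but the article gives no figure for lateness.
- *The error favours SHER.* Pre-randomisation tests should be balanced by randomisation, and testing history (never or ever) was added as a stratification factor.

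An article may also leave date fields and event derivation to the analysis plan. That excuses missing detail, but not two stated rules that disagree.

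**Conclusion.** The contradiction stands. The article gives two incompatible recall periods for its primary outcome, which differ at 3 weeks, 7.5 months and 9 months. Under one, about 77% of the 3-week look-back precedes randomisation. Under the other, a model that takes only the 9-month survey as its last point misses months 6 to 7.5, assuming the 6-month follow-up means the 9-month column.

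The consequence is conditional and of unknown size: non-differential dilution if 3-week reports enter the endpoint under Table 1, or lost events if the 7.5-month report is left out under Outcome Measures. The power figures illustrate direction only. The point deserves correction because it concerns the primary outcome and can be settled before results are seen, not because a large loss has been shown.

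**What to change.** Before analysis:

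1. Define the primary event as an HIV test dated after randomisation and up to month 9, derived from all follow-up reports, including those at 3 weeks and 7.5 months.
2. Use one recall rule at every follow-up: since the last completed survey that asked about HIV testing, or since enrolment for the first. Keep the three-month look-back for baseline only.
3. If any 3-week reports were collected with three-month wording, count them only when the reported date or the uploaded proof falls after randomisation.
4. Reword the Table 1 row to match, and state which Table 1 columns the model's 3-month and 6-month follow-ups refer to.

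The cost is some date checking of reports already collected, helped by the proof that participants are already asked to upload, and a wording change. No extra participants are needed.
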